### **Hypothesis:**

The BSMART intervention (SBIRT and varenicline) will

- i. Increase the proportion of smokers able to quit smoking
- ii. Increase the number of attempts to quit smoking
- iii. Increase the length of abstinence in failed quit attempts
- iv. Decrease the number of cigarettes smoked every day
- v. Decrease the number of days of using combustible products within the past month
- vi. Decrease the number of days of using combustible products within the past three months in people exposed to the intervention as compared to people in the control phase

**Potential Impact:** Addressing the syndemic between tobacco use and HIV infection in a coordinated manner aligns with the NIH HIV/AIDS priorities for effective cancer control among PLWH in a high HIV prevalence setting. This study is significant because it integrates smoking cessation interventions, which are lacking in sub-Saharan Africa (SSA), into a real-world HIV care system that has been underpinned by a robust PEPFAR/CDC program and leverages long-standing partnerships with Ministry of Health and Wellness and the University of Botswana's Anti-tobacco Network for population, health system, and policy level impact.

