#### Secondary Outcomes:

- Quit attempts
- Length of successful quitting during each attempt
- Number of cigarettes currently smoked, and
- Number of days of using combustible tobacco products for at least 24 hours within the past month and the last 3 months.

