## Ensuring Data Quality

The approach to data quality is based on the following key points:

| Components of data quality | Approach                                                  |
|----------------------------|-----------------------------------------------------------|
| 1. Data Completeness       | Minimum missing values                                    |
| 2. Data Accuracy           | Matching values in the database with original observation |
| 3. Data Precision          | Defining units and measurability                          |
| 4. Timely collection       | Minimal time loss between observation and recording       |
| 5. Data Verification       | Independent assessment or monitoring                      |
| 6. Data Tracing            | Logging actions taken while handling the data             |

Above points will be ensured as follows:

a) Data Validation and Queries

The data manager will assess data quality using REDCap's Data Quality module. Any identified issues will either be corrected or documented in the study data handling manual. Electronic data collection forms will be programmed with online validation checks. These checks will:

- Alert data entry users to missing data
- Check that numeric variables and dates are within reasonable ranges
- Check for consistency within the data

b) Data Quality Audit

At intervals throughout the study a subset of entered data will be compared with the original data collection forms. The number of compared forms and error counts will be recorded in order to measure the percentage data entry error rate.

These audits will be conducted using random samples as follows:

- 10 of the first 100 subjects
- 20 of the first 200 subjects
- 75 of the total 750 subjects

The error rate for study data will be maintained below 0.1%. If error rates remain high for three consecutive samples the team will need to consider alternative remedies in order to bring the error rate within acceptable limits.

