| We are going to ask you some questions about your smoking behavior                                                                                                                       |                                                                                       |                                                                                                                                                                                                                |
| 1.                                                                                                                                                                                       | Have you smoked a cigarette, even a puff, during the past 30 days?                    |  Yes
 No                                                                                                                                                    |
| 2.                                                                                                                                                                                       | Have you smoked a cigarette, even a puff, during the past 7 days?                     |  Yes
 No                                                                                                                                                    |
| 3.                                                                                                                                                                                       | Are you currently smoking regularly?

If yes, how many cigarettes a day? |  Yes
 No
_____ cigarettes                                                                                                                                |
| 4.                                                                                                                                                                                       | How many days of the week do you smoke?                                               |  7
 6
 5
 4
 3
 2
 1 |

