| 5. | 
Since your last study visit, have you ever quit for a period of at least 24 hours?
 
If No, skip to Q9.
                                                                                                                                                                                                                                                                                    |  Yes
 No                                                                                                                                                                                                                                                                                                   |
| 6. | 
Since your last study visit, how many times have you quit for at least 24 hours? (If more than 9 times, put 9)
                                                                                                                                                                                                                                                                                         | 
_____ times
                                                                                                                                                                                                                                                                                                                                            |
| 7. | 
After your most recent quit attempt, how long did you stay off cigarettes?
                                                                                                                                                                                                                                                                                                                             |  1-2 days
 A week
 2-4 weeks
 Over 4 weeks                                                                                                                                                                                                           |

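### The only follow-up question that counts smoking days runs from 7 to 1 with no zero and no skip, so abstainers and less-than-weekly smokers have no valid answer

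*Protocol*

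**What the plan says.** The Hypothesis section of the Protocol states that the intervention will "Decrease the number of days of using combustible products within the past month", and it makes the same claim for the past three months. The Secondary Outcomes list repeats this as "Number of days of using combustible tobacco products for at least 24 hours within the past month and the last 3 months".

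The follow-up data come from Appendix B4, completed at weeks 4, 12 and 24 in both phases (Tables 2 and 3). Its opening questions run as follows:

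- Question 1: "Have you smoked a cigarette, even a puff, during the past 30 days" – Yes or No, with no skip.
- Question 2: "Have you smoked a cigarette, even a puff, during the past 7 days" – Yes or No, with no skip.
- Question 3: whether the person currently smokes regularly, with the sub-item "If yes, how many cigarettes a day". The condition governs only that sub-item.
- Question 4: "How many days of the week do you smoke" – boxes for 7, 6, 5, 4, 3, 2 and 1.
- Question 5: whether the person has quit for at least 24 hours since the last visit. It carries the first printed skip, "If No, skip to Q9".

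The same days-of-the-week item, with the same seven boxes, opens the intake questionnaire (Appendix B3).

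**The concern.** At intake the 7-to-1 list causes no difficulty, because eligibility requires a self-reported daily smoker. At follow-up the same list is put to people who may have stopped. A participant who answers No to Questions 1, 2 and 3 is still asked Question 4 as the form is printed, and none of its boxes is true. The same holds for someone who smokes less often than once a week.

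The form suggests an oversight. The personal-goal item was adapted between intake and follow-up, gaining an option for people who have already quit and its own branching. The days item was carried over unchanged.

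At stake is the days-of-use comparison. The people without a valid answer are those the intervention aims to produce, and more of them are expected in the implementation phase than in the control phase. How their blanks are treated then decides whether quitting counts in the comparison. The protocol states no rule for this; a statistical analysis plan, not shown here, may do so.

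**Working it through.** **Is there another source of smoking days?** The rest of Appendix B4 covers quit attempts, symptoms, goals and confidence. The stages-of-change form, medication adherence form, side-effects checklist and interview guides were also checked. None gives a follow-up count of days smoked, so Question 4 is the only one.

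**How many people have no valid answer at week 24?** The protocol gives no figure to reproduce, so this is an illustration on its own planning inputs:

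- 375 participants per phase (Study Design).
- Control abstinence of 10%, range 8% to 14%; an increase of 10 points; 5% loss to follow-up (Power and Sample size).

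Followed per phase: 375 × 0.95 = 356.25, or 712.5 in all.

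| Abstinent, control / implementation | Control | Implementation | Total | Share |
|---|---|---|---|---|
| 10% / 20% | 35.6 | 71.3 | 106.9 | 15% |
| 8% / 18% | 28.5 | 64.1 | 92.6 | 13% |
| 14% / 24% | 49.9 | 85.5 | 135.4 | 19% |
| 10% / 18% (the 8-point increase named in the study objectives) | 35.6 | 64.1 | 99.8 | 14% |

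These counts cover abstainers only. Less-than-weekly smokers come on top, but the documents give no basis for a number.

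**What does the handling of blanks do to the comparison?** Let A be the proportion abstinent and s the days per week smoked by those who continue. Assume s is the same in both phases. With abstainers counted as zero, mean days = (1 − A) × s.

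- s = 7: 0.90 × 7 = 6.3 against 0.80 × 7 = 5.6, a difference of −0.7.
- s = 5: 0.90 × 5 = 4.5 against 0.80 × 5 = 4.0, a difference of −0.5.

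With abstainers blank and dropped, both phases have mean s and the difference is 0 for either value of s.

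**What can be recovered?** A blank at Question 4 with No at Question 2 points to zero cigarette days in the past week. Two limits apply. Questions 1 and 2 ask about a cigarette, whereas the outcome is combustible tobacco, and intake Question 10 records cigars and waterpipe. Also, a person answering Yes to Question 1 and No to Question 2 has zero for the week but an unknown number of days for the month.

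**Does Question 4 match the outcome?** It asks about days of the week with no recall window, while the outcome is days in the past month and the last 3 months. A zero box closes the response gap but does not by itself make the item measure the named outcome.

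**The case against.** The strongest reply is that the information is largely on the form already. Questions 1 and 2 stand directly above Question 4, so an analyst can identify most abstainers and set them to zero. Nothing in the protocol plans to drop them, and the handling of this outcome may be set out in the statistical analysis plan. This stands, and it limits the harm to what happens if no such rule is applied, plus the cases that Questions 1 and 2 cannot settle.

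It may also be said that the form is completed on a tablet, so an unprinted branch could hide Question 4 from abstainers. The methods text does limit the number of cigarettes to people who are not abstinent. But it does not mention days smoked, and other skips are printed on this form while this one is not.

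Three stronger readings are tempting, and the documents do not support them.

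- **That the primary endpoint is compromised.** It rests on self-reported 7-day abstinence confirmed by expired CO below 6 ppm, and Question 4 plays no part.
- **That staff would enter 1 for a quitter.** The data checks will "Alert data entry users to missing data", but an alert is not a mandatory field, and the same list includes a check for consistency within the data, which could catch a 1 beside No at Question 2. Even if every quitter were entered as 1, the differences above would shrink only from −0.7 to −0.6 (6.4 against 5.8) and from −0.5 to −0.4 (4.6 against 4.2).
- **That the whole effect on days is lost.** This needs abstainers to be dropped despite their recorded status, and continuing smokers to smoke equally often in both phases. Any reduction among continuing smokers would still show.

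**Conclusion.** The point holds as a defect in a fixed data-collection form. Abstainers and less-than-weekly smokers have no valid answer to the only follow-up item that counts smoking days. On the planning rates with 5% loss this concerns about 107 of 712 followed participants at week 24 (15%; 93 to 135 across the control range of 8% to 14%), with twice as many in the implementation phase as in control. Those counts take the planned abstinence rates as a stand-in for the number without a valid answer.

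The consequence is conditional. If blanks are dropped, the comparison is restricted to continuing smokers, a group selected by the outcome, and the contribution of quitting disappears: 0.7 days a week if continuing smokers smoke 7 days, 0.5 if they smoke 5, assuming the same frequency in both phases. If blanks are filled from the neighbouring answers, most of this is avoided. The harm is confined to a secondary outcome, but the form should be corrected because the remedy is cheap.

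**What to change.** 1. **Form.** At the least, add a zero option and a less-than-one-day-a-week option to Appendix B4 Question 4. Preferably, replace it with the number of days of any combustible tobacco use in the past 30 days, and since the last visit or in the past 3 months, both allowing zero. That also brings the item into line with the Hypothesis section and the Secondary Outcomes list.
2. **No auto-fill from Question 1 alone.** That question covers cigarettes only. Auto-filling zero from it could overwrite cigar or waterpipe use, and it would miss people who answer Yes to Question 1 and No to Question 2.
3. **Records already collected.** Set a blank Question 4 to zero where Question 2 is No and no other combustible use is recorded. Document the rule.
4. **Analysis.** Compare days of use in all participants, with abstainers counted as zero.

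The cost is two answer options, or one replaced item with two recall windows, in REDCap, plus a short recoding rule. Neither the visit schedule nor the primary endpoint changes.

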### Follow-up

Research assistants will fill out follow-up smoking questionnaires at weeks 4, 12 and 24 after the patient receives the SOC brochure. Participants will be provided with breath CO measurements using CO Check+

(coVita) at baseline and then weeks 12 and 24 after enrollment. Participants will also be asked to respond to a semi-structured interview at week 24 that explores challenges to smoking cessation, barriers experienced by participants and reasons for success in those who were able to quit successfully.

| Table 2: Participant Timeline- Control Phase |                    |                                           |        |         |         |
|----------------------------------------------|--------------------|-------------------------------------------|--------|---------|---------|
|                                              | Responsible person | 1 st clinic visit/
Baseline | Week 4 | Week 12 | Week 24 |
| Screening of participants                    | LHW case manager   | X                                         |        |         |         |
| Informed Consent                             | Research Assistant | X                                         |        |         |         |
| Enrollment in BSMART study                   | Research Assistant | X                                         |        |         |         |
| Intake Smoking Questionnaire                 | Research Assistant | X                                         |        |         |         |
| Receipt of SOC brochure                      | LHW case manager   | X                                         |        |         |         |
| Follow-up smoking questionnaire              | Research Assistant |                                           | X      | X       | X       |
| Stages of change                             | Research Assistant | X                                         | X      | X       | X       |
| Breath CO                                    | Research Assistant | X                                         |        | X       | X       |
| Semi-structured Interview                    | Research Assistant |                                           |        |         | X       |

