### Estimating process and outcome measures

All procedures will be conducted according to the local standards of routine clinical care. The following measures will be utilized:

1. **Baseline Demographic Information:** Baseline information will be abstracted from the HIV medical records and collected using a questionnaire. Baseline information will include demographics, medical history, laboratory values measured as part of HIV care (e.g. viral load, CD4), antiretroviral (ARV) history and ART treatment regimen (for current patients), and ART treatment start date. Because of high viral load suppression and high retention rate in this population, we will not be analyzing HIV treatment variables as mediators or outcomes.
2. **5”A”s (SBIRT) checklist:** This checklist will be completed by the LHW case managers and will serve to document the delivery of the intervention. A 10% random sample of the completed 5”A”s checklist will be reviewed by [name] during the time that a site is engaged in the intervention to ensure fidelity to the study intervention.
3. **Intake Smoking History Questionnaire** will measure length of smoking, use of other tobacco products, quit attempts, length of longest quit attempt, and smokers in the immediate living environment.
4. **Follow-up Smoking Use Questionnaire** will measure 7-day and 30-day point prevalence abstinence, number of cigarettes smoked (if not abstinent), stage of change and readiness to quit (if not abstinent), length of longest period of abstinence since last evaluation, use of varenicline, side effects, reasons for using or not using varenicline, and length of varenicline use.

5. **Stages of Change Algorithm** and **the Readiness Ruler**, will be used at baseline and follow-up to determine each individual's stage of change for quitting tobacco.
6. **Smoking Abstinence**: Abstinence will be based on self-reported 7-day point prevalence abstinence confirmed by expired CO < 6 ppm. Abstinence criteria must be met in participant Month 6 or at an earlier study week and maintained through participant Month 6 to be considered a responder. We will use coVita CO Smokerlyzer, a single-breath point-of-care tool designed specifically for use in smoking cessation programs and clinics.

For those who agree to be treated with varenicline:

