Appendix B4: Follow-Up Smoking Questionnaire

**BSMART**

**Follow-up Smoking Questionnaire**

|                            |                        |
|----------------------------|------------------------|
| Researcher ID:      | Participant ID: |
| District:           | Facility:       |
| Date: (dd/mon/yyyy) |                        |

|                                                                                                                                                                                          |                                                                                       |                                                                                                                                                                                                                |
|------------------------------------------------------------------------------------------------------------------------------------------------------------------------------------------|---------------------------------------------------------------------------------------|----------------------------------------------------------------------------------------------------------------------------------------------------------------------------------------------------------------|
| 
Please answer these questions based on your experiences with smoking since the last time we saw you. When you select an answer, I will enter it on the form in the tablet.
 |                                                                                       |                                                                                                                                                                                                                |
|                                                                                                                                                                                          | Question                                                                       | Response                                                                                                                                                                                                |

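### The follow-up smoking form cannot record a quit that began before the previous visit and is still continuing, so attempts and lengths depend on how one question is read

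*Protocol*

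**What the plan says.** The form in Appendix B4 opens with a recall frame: "Please answer these questions based on your experiences with smoking since the last time we saw you". Under Follow-up (control phase) the protocol states that "Research assistants will fill out follow-up smoking questionnaires at weeks 4, 12 and 24", and Table 3 gives the same weeks for the intervention phase.

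The items on quitting are:

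- **Q5:** "Since your last study visit, have you ever quit for a period of at least 24 hours", with the routing instruction "If No, skip to Q9".
- **Q6:** "Since your last study visit, how many times have you quit for at least 24 hours", capped at 9.
- **Q7:** "After your most recent quit attempt, how long did you stay off cigarettes". The answers are 1-2 days, a week, 2-4 weeks, and over 4 weeks.
- **Q8:** severity of problems while trying to quit. It is also skipped after a No to Q5.

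The Secondary Outcomes list names quit attempts and "Length of successful quitting during each attempt". Item 4 under Estimating process and outcome measures says that the form yields the "length of longest period of abstinence since last evaluation". In the Hypothesis section, ii expects more quit attempts under the intervention, and iii expects longer abstinence in attempts that failed.

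For varenicline users, the section on provision of varenicline schedules the quit date for day 8, before the first follow-up form is due.

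**The concern.** Q5 to Q7 are worded for someone who was smoking at the previous visit. They have no answer for a person who had already quit by then and has stayed off. There is no still-abstinent option, no quit date and no coding instruction, so the interviewer must choose between two defensible readings.

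- **Literal reading:** only a quit begun since the last visit counts.
- **Interval reading:** being off for at least 24 hours at any time in the interval counts.

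The readings give different attempt counts and different lengths for the same person. The affected group is the sustained quitters, whom the intervention is meant to make more numerous, so the effect need not cancel between phases. At stake are two secondary outcomes and the hypotheses they serve. A quit date that was never collected cannot be rebuilt at the analysis stage.

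**Working it through.** No stated figure needs reproducing; this is a question of form logic.

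**Step 1. Trace one participant.** Inputs: quit on day 8 (Provision of varenicline; assume the first dose is at enrolment), no smoking afterwards, forms on days 28, 84 and 168. Time off at each form is 28 - 8 = 20 days, 84 - 8 = 76 days and 168 - 8 = 160 days.

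| Form | Literal reading | Interval reading |
|---|---|---|
| Week 4 | 1 attempt, 2-4 weeks | 1 attempt, 2-4 weeks |
| Week 12 | No; Q6-Q8 skipped | 1 attempt, over 4 weeks |
| Week 24 | No; Q6-Q8 skipped | 1 attempt, over 4 weeks |
| Sum of attempts | 1 | 3 |

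The literal sum is right, but the length is frozen at the week 4 category for a 160-day quit. On the interval reading the length moves on but the count triples.

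**Step 2. Which visit is the last one?** Intervention participants on varenicline also attend weekly for medication. If the week 3 pick-up (day 21) is taken as the last study visit, a day 8 quit precedes it. The literal answer at week 4 is then No as well: 0 attempts and no length on any form. Control participants have no such visits (Table 2), so this ambiguity arises only in the intervention phase.

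**Step 3. Failed attempts.** Q7 alone does not say whether the quit has ended. Suppose a quit reported at week 4 ends in relapse before week 12, with no new attempt. On the literal reading Q5 at week 12 is No, and the length of that failed attempt stays at its week 4 value. This is the quantity in hypothesis iii.

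**Step 4. Can other items settle the reading?** Q1 covers 30 days. The intervals before the week 12 and week 24 forms are 84 - 28 = 56 and 168 - 84 = 84 days, which leaves 26 and 54 days that Q1 does not cover. A participant abstinent at both forms with Q5 = Yes may be a continuing quitter or one who relapsed and quit again.

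**Step 5. Does the direction depend on the reading?** This is an illustration only. Take sustained quitters as A = 0.10 (control) and 0.20 (implementation), from Power and Sample size. Assume that all of them quit before week 12, and that a share q of everyone else attempts in weeks 12-24, equal in both phases. Share with Yes at week 24:

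- Literal: (1 - A)q. For q = 0.3, 0.5, 0.7: control 27, 45, 63%; implementation 24, 40, 56%; difference -3, -5, -7 points.
- Interval: A + (1 - A)q. Control 37, 55, 73%; implementation 44, 60, 76%; difference +7, +5, +3 points.

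These are two different quantities, and neither is the truth against which the other errs. The form does not say which one it collects.

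For attempts summed over the three forms, compare with counting each quit once, assuming that all sustained quitters start before week 4:

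- Interval reading throughout: (0.20 - 0.10) x 2 = +0.2 attempts per participant in favour of implementation. If control quits all began after week 12, it would be 0.20 x 2 - 0 = +0.4.
- Literal, last questionnaire as reference: 0.
- Literal, week 3 pick-up as reference, if every sustained quitter in the implementation phase takes varenicline: 0.20 x (-1) = -0.2.

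**The case against.** The strongest reply is that the rest of the form and the visit recognise the abstainer. Q1 and Q2 record no smoking in 30 and 7 days, Q9 has an option for people who have already quit, the staging tool places them in the action stage, and breath CO is taken at weeks 12 and 24. This stands. A reader might infer that a sustained quitter is stored exactly like a smoker who never tried. The document does not support that: No on Q1, No on Q5 and the first option on Q9 together identify a continuing quitter read literally. None of these items records an attempt or a length, however, and the staging tool's own count of attempts is asked of smokers only.

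A reader might also infer that the attempt is lost altogether, or that a lower share of attempters at week 24 on the literal reading is an error. Neither follows. The attempt may stand correctly once on an earlier form, and under a count-once rule a sustained quitter makes no new attempt in weeks 12-24, so the lower share is right for new attempts.

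How the forms are combined may be set in an SAP that is not shown, and research assistants are trained on the tools. Triple counting therefore needs both the interval reading and plain summing, neither of which the protocol prescribes. That limits the claim about counts. It does not rescue the length: varenicline users have a scheduled quit day, but it need not be the actual one, and no quit date is scheduled for control participants. Finally, people who never relapse have no failed attempt and do not bear on hypothesis iii. Those who relapse after a form has been completed do.

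**Conclusion.** The point holds as a data-capture gap in an instrument that the protocol fixes. Q5 to Q7 cannot record a quit that spans a visit. Depending on the reading, its length is frozen early or the quit is recorded again at each form, and Q7 alone cannot separate an ongoing quit from a failed one.

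The consequences are confined to the secondary outcomes on attempts and length and to hypotheses ii and iii. The primary endpoint is untouched. No single bias figure is justified: the illustrations run from -0.2 to +0.4 summed attempts per participant, and from -7 to +7 points in the share with Yes at week 24. All of them rest on assumed quit timing, attempt rates and uniform reading by interviewers. What is firm is that the direction depends on a reading that the form leaves open, that part of the ambiguity cannot be resolved from the stored data, and that the lost lengths cannot be recovered later. The form should be changed.

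**What to change.** 1. In Q5 and Q6, make the reference point the last smoking questionnaire instead of the last study visit, so that medication pick-ups do not reset the interval.
2. Where an earlier quit is already on record, ask first whether the participant has smoked at all since that questionnaire. If not, code a continuing earlier quit, add no new attempt and go to Q8. Restricting the branch in this way keeps a quit made soon after enrolment countable once at week 4.
3. Record the start date of the most recent quit on the form where it is first reported, and add a still-abstinent option to Q7. Length can then be computed, and ongoing quits separated from failed ones. When a quit on record has ended since the last form, record when it ended.
4. State in the outcome definition that each attempt counts once, at the form where it began.

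The cost is two or three short items with branching in REDCap and a sentence in the outcome definition. No extra visit or staff is needed. Forms completed before the change would remain only partly repairable.
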